### Usual care condition

Patients randomized to the usual care condition will receive usual implementation for nutrition counseling, which means that a member of the clinic team will refer patients to a dietitian when they deem it necessary. Patients in the usual care condition will receive the same educational brochure that the intervention group receives about eating problems that occur during cancer treatment targeted for gastric and esophageal cancer patients. Nutrition education is considered a part of standard of care; therefore, the educational booklet developed will also be provided to the control group.

### Retention strategies

To optimize retention, patients can choose to receive the intervention in a format they prefer (app or paper log). We will engage caregivers in implementation of patient-mediated strategies when available and provide training, technical assistance, and follow-up. Study staff will train patient participants, call all patients within 3–5 days of study enrollment to confirm understanding of what is being asked of them and see if they need any help. Study staff will help patient participants troubleshoot any technical challenges (e.g., REDCap survey not working) and refer patients to additional resources when needed (e.g., Zoom help line managed by the Cancer Center). Patients who opt in for study-related text messaging will receive reminders for upcoming dietitian appointments and study-related tasks (e.g., patient-reported outcome reporting). We will provide patients with summaries about their study progress (e.g., 75% of dietitian visits are completed).

### Measures

#### Study assessment schedule

Patients will receive a survey at baseline, 1 month, 3 months (end of intervention), and 6 months. Data will also be obtained from patient-reported information collection (app or paper log), and the EHR. Patients will have the option to participate in a one-time exit interview to provide feedback on the intervention (nutrition counseling) and the patient-mediated implementation strategies (e.g., patient-reported information collection, education, question prompt list). The study team will also collect data from caregivers and healthcare providers (e.g., dietitians, physicians, nurses) who assisted with study implementation through a one-time exit interview. Patient participants will receive $25 gift cards for each study assessment completed and a $50 gift card for interview participation. Study assessments and materials including surveys and interview guides have been translated and are available in Spanish and English.

### Primary outcomes

Primary outcomes for this pilot study are feasibility and acceptability. Feasibility will be defined based on (1) recruitment rate (proportion of eligible patients who consent); (2) study assessment completion; (3) intervention adherence and engagement (app or paper log use, participation in dietitian visits, use of question prompt list and handout); (4) retention rate (proportion of patients who are retained at the end of the intervention); and (5) reasons for declining to participate and study attrition. Acceptability will be measured based on the proportion of patients who report satisfaction with the overall intervention and individual intervention components. Outcomes will be measured through study screening logs and administrative data (e.g., completed assessments in REDCap). We will compare feasibility and acceptability outcomes observed in the proposed study against pre-planned benchmarks (Table 3), which were established based on prior studies in similar patient populations [103–108]. 

### Secondary implementation outcomes

The study will also collect preliminary data on implementation outcomes that may be associated with the STRONG program based on the RE-AIM framework [62] including reach (proportion of target population that was reached by the intervention), adoption (proportion of providers who referred patients to the study), implementation (fidelity, contamination, adaptation), and maintenance (impact of the intervention at six months). Fidelity will be measured to determine if key elements of the intervention were delivered (e.g., establishing individual calorie goals, discussing patients’ goals for improving nutrition) and how much of the intervention was delivered (e.g., length of dietitian visits, participant use of strategies recommended by the dietitian). We will document potential contamination (ask usual care patient participants about use of patient-mediated strategies), and unplanned intervention modifications using the FRAME documentation tool [109]. 

### Qualitative feedback

A subset of patient participants (*N* = 20; ~10 per site) will be asked to provide feedback on the quality of the intervention (e.g., nutrition counseling) and strategies (e.g., question prompt list, patient-reported information), and any barriers/facilitators to intervention uptake and/or strategy implementation. Caregivers and healthcare providers who supported implemented (*N* = 25; ~5 per group [dietitian, physician, nurse, caregiver]) will be asked to provide feedback on the implementation strategies and barriers and facilitators to implementation. The interviews will be led by a staff member trained in qualitative methods using a semi-structured interview guide based on the TDF [69–71]. The interviews will be approximately 30–45 min in length, recorded, and transcribed verbatim.

### Secondary effectiveness outcomes

The study will collect preliminary data on patient and service delivery outcomes that may be associated with the STRONG program. Nutritional status will be measured using the PG-SGA short-form and serve as the primary effectiveness outcome in a future definitive trial [89, 90]. A change in score of 4 points is considered clinically meaningful [89, 90]. We will examine changes in the proportion of patients who are categorized as malnourished via the PG-SGA based on cutoffs established in prior research [110]. We will assess other indicators of nutritional status including changes in weight [111] and skeletal muscle mass. Skeletal muscle mass will be estimated from routinely collected CT scans and categorized based on previously established cutoffs for sarcopenia [112]. We will use CT ‘slices’ from the midpoint of the third lumbar vertebrae for analyses. We will blind CT assessors to study arm. Quality of life will be measured using 1) the Functional Assessment of Cancer Therapy General scale [113]; 2) the Functional Assessment of Anorexia/Cachexia Therapy subscale [114]; and 3) the FACT–esophageal and gastric cancer subscale [115, 116]. Change in quality-of-life scores will be measured using established minimal clinically important differences (MCIDs) when available [117–119]. We will measure planned versus received systemic therapy and/or radiotherapy to define treatment delay (yes/no), dose reduction (yes/no), or treatment discontinuation (yes/no). To measure survival, we will obtain vital status from the cancer registry to estimate overall survival (time from random assignment to death from any cause) and progression-free survival (time from random assignment to disease progression or death from any cause). We will measure service delivery outcomes including the timeliness of dietitian referrals (e.g., median time from diagnosis to first referral) and patient perceptions about the patient-centeredness of nutrition care delivery using the Patient-Centered Communication in Cancer Care Short Form (6-item) [120]. 

### Mechanisms of change

We will measure two factors that may serve as mechanisms of change and help explain the potential impact of STRONG on improved implementation of nutrition counseling. First, we will measure patient activation (knowledge, skills, and confidence in managing health and healthcare) via the Patient Activation Measure (13-item) [121, 122]. Second, we will measure patient self-efficacy for communicating with dietitians via the Perceived Self-Efficacy Scale [123]. 

### Participant and treatment characteristics

Participant characteristics will be captured via the baseline survey and include factors that may affect engagement with the patient-mediated implementation strategy (e.g., sex, age, race/ethnicity, language preference, digital and health literacy). Clinical characteristics that may affect nutritional status (e.g., cancer stage, comorbidities) will be abstracted from the EHR. Treatment characteristics (e.g., single vs. multi-modal treatment, treatment type, dose planned versus dose received) will be abstracted from the EHR. Nutrition-related interventions and date of delivery (e.g., feeding tube) will be abstracted.

### Data analyses

#### Analytic approach

The primary purpose of this trial is to estimate feasibility outcomes against pre-planned benchmarks to prepare for a future fully powered trial. A secondary goal of this pilot is to explore the preliminary effects of the intervention on patient outcomes. We will use an intent-to-treat approach and analyze all randomized patientsto explore real-world effectiveness and conduct additional per-protocol analysis to explore effects in patients who adhered to the study protocol. We will examine potential sources of bias (e.g., selection bias, differential attrition) and the amount and pattern of missing data (e.g., by arm/time) and adjust the statistical approach as needed. Plans for each Aim are described below.

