**Table 3 Tab3:** Pre-planned benchmarks for pilot trial

Measure	Benchmark
**Recruitment**: Proportion of eligible patients who consent to participate	≥ 50%
**Data Completion**: Proportion of patients who complete all study assessments	≥ 70%
**Retention**: Proportion of patients who are retained at the end of the intervention	≥ 85%
**Counseling adherence**: Proportion of patients who attend the majority (3/4) dietitian visits	≥ 70%
**Logging adherence**: Proportion of patients who log food intake and symptoms ≥ 3 days a week for study period	≥ 70%
**Question prompt list usage**: Proportion of patients who report using question prompt list	≥ 70%
**Educational brochure usage**: Proportion of patients who report using educational brochure	≥ 70%
**Fidelity**: Dietitian adherence to prescribed elements of counseling outlined in checklist	≥ 80%
**Acceptability**: Proportion of patients who report high satisfaction with intervention	≥ 80%
**Perceived usefulness**: Proportion of patients who report question prompt list was useful for patient-dietitian discussions	≥ 80%

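### The per-protocol analysis selects on post-randomisation adherence that is defined mainly by STRONG tasks, so its between-arm comparison is not randomised and plausibly favours STRONG

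*Protocol article*

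**What the plan says.** Under Analytic approach, the article leads with intent-to-treat: "We will use an intent-to-treat approach and analyze all randomized" patients. It then adds that the team will "conduct additional per-protocol analysis to explore effects in patients who adhered to the study protocol". It says nothing about which arm the restriction applies to or how early deaths and stoppers are classed.

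Adherence is described elsewhere. Primary outcomes lists log use, dietitian visits, and use of the prompt list and handout. Table 3 sets 70% benchmarks for counseling ("Proportion of patients who attend the majority (3/4) dietitian visits"), for logging at least three days a week over the study period, and for prompt-list and brochure use.

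Under Intervention condition, STRONG patients have one visit before treatment and bi-weekly visits for 12 weeks. In usual care, "a member of the clinic team will refer patients to a dietitian when they deem it necessary". Elements that do reach usual care are the survey schedule, the brochure ("Patients in the usual care condition will receive the same educational brochure that the intervention group receives") and a contamination record ("We will document potential contamination (ask usual care patient participants about use of patient-mediated strategies").

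**The concern.** Adherence is observed after randomisation and may share causes with the outcome. A patient who misses bi-weekly visits or stops logging may be in hospital, progressing or dying. If such patients leave one arm while their counterparts stay in the other, the groups differ in prognosis even when the strategy does nothing.

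The point is not that a cut-off is missing, since an analysis plan may supply one. The stated comparison, effects among adherers, selects on behaviour that mostly only STRONG patients can show, and a cut-off alone would not cure that. Survival is the more exposed outcome. Secondary effectiveness outcomes times overall and progression-free survival from random assignment, and a patient must be alive to attend visits or keep a log.

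The effect estimates are exploratory, but the pilot is meant to give preliminary estimates that support a definitive trial. An inflated adherent-only estimate beside the intent-to-treat result could mislead that planning.

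**Working it through.** **The plan's own figures.** 80 × 0.85 = 68, or 34 per arm, as stated. The stated precision of ±2.4–2.8 points is reproduced by a baseline-adjusted comparison, 1.96 × SD × √(1 − 0.55²) × √(2/34) = 2.38 (SD 6) and 2.78 (SD 7). These give the scale for what follows.

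**PG-SGA, no true effect, restriction in STRONG only**

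Inputs from the article: SD 6–7 (Sample size considerations) and adherence p = 0.70 (Table 3 benchmark). Assumed: a correlation ρ between the propensity to adhere and a better outcome, and normality.

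Bias = ρ × SD × φ(z_p)/p. With z = 0.524 and φ(z) = 0.348, the multiplier is 0.348/0.70 = 0.497. On the benchmark, 28 of 40 STRONG patients are compared with 40 of 40 in usual care.

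| Restriction | Multiplier | ρ = 0.1 | ρ = 0.3 | ρ = 0.5 |
|---|---|---|---|---|
| STRONG only, p = 0.70 | 0.497 | 0.30–0.35 | 0.89–1.04 | 1.49–1.74 |
| STRONG 0.70, usual care 0.85 | 0.497 − 0.274 = 0.222 | 0.13–0.16 | 0.40–0.47 | 0.67–0.78 |

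Each range runs from SD 6 to SD 7. The second row takes 0.85 from the retention benchmark as a filter that usual care could share, with the same ρ in both arms. A negative ρ reverses every sign. The formula uses the raw SD; with the residual SD after baseline adjustment (× 0.835), the first row becomes about 0.25–0.29, 0.75–0.87 and 1.24–1.45.

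**Survival, no true effect**

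- One initial visit plus bi-weekly visits over 12 weeks is 1 + 6 = 7 visits, at about weeks 0, 2, 4, 6, 8, 10 and 12.
- If three quarters applies to all seven, 0.75 × 7 = 5.25, so six visits are needed and the sixth falls at week 10 at the earliest.
- If it means three of four visits, the third falls at week 4 at the earliest.

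Assume a constant hazard λ, equal in both arms, 26 weeks of follow-up, 6-month mortality of 5%, 10% or 20% (not in the article), and deaths before week w removed from STRONG only. Everyone left in STRONG contributes w event-free weeks, so

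rate ratio = A/(w + A), with A = (1 − e^(−λ(26 − w)))/λ and λ = −ln(1 − mortality)/26.

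When mortality is low this tends to (26 − w)/26.

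| Survival required to | Low-mortality limit | 5% | 10% | 20% |
|---|---|---|---|---|
| Week 4 | 22/26 = 0.85 | 0.84 | 0.84 | 0.83 |
| Week 10 | 16/26 = 0.62 | 0.61 | 0.61 | 0.60 |
| Week 12 | 14/26 = 0.54 | 0.54 | 0.53 | 0.52 |

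A Cox simulation of the week-10 case gave hazard ratios of 0.59–0.61. Few deaths are involved: at week 12, about 0.9, 1.9 or 3.9 of 40 STRONG patients are removed.

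**The case against.** A reader might infer that only STRONG patients can be dropped, that usual care has nothing to adhere to, and that early deaths will be excluded. The article states none of these. Its phrase is adherence to the study protocol, which is wider than intervention adherence. Surveys and the brochure are common to both arms, and contaminated controls could be excluded. Those facts stand, so the restriction falls mainly, not solely, on STRONG. They do not restore comparability. Survey completion is a different filter from attending visits and logging, and dropping contaminated controls would select on yet another post-randomisation behaviour.

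It would also be too strong to say that the result is biased towards STRONG. For PG-SGA the direction depends on ρ, which the article does not give; if sicker patients attend more, the bias goes the other way. The survival ratio of 0.6 needs six of seven visits and early deaths removed from STRONG alone. The article does not name survival as a per-protocol outcome, and with about 2–8 deaths in an arm of 40 any hazard ratio would be very imprecise.

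The article has safeguards. Intent-to-treat leads, the effect analyses are secondary ("A secondary goal of this pilot is to explore the preliminary effects of the intervention on patient outcomes"), and "We will examine potential sources of bias (e.g., selection bias, differential attrition") the approach will be adjusted as needed. This limits the consequences. But patients excluded by definition are not lost to follow-up, and the planned mixed models cannot use patients who have been taken out of the analysis set.

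The complier-average estimate has its own weakness. STRONG also works through logging, the dashboard and the prompt list, so an effect of assignment outside the visits is plausible. That stands and must be stated with the estimate.

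**Conclusion.** The point holds in limited form. The planned comparison among adherers is not protected by randomisation, because the adherence the article defines consists mainly of STRONG tasks.

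For PG-SGA, the plausible spurious benefit is 0.3–1.7 points, assuming ρ of 0.1–0.5, 70% adherence and restriction in STRONG only. It roughly halves if usual care is filtered at 85%. The upper end is material against a half-width of 2.4–2.8 points and a 4-point meaningful change; the lower end is not. The sign is likely but not certain.

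For overall and progression-free survival, the immortal-time component runs only towards STRONG: a null ratio of about 0.6 under a week-10 requirement and about 0.84 under a week-4 requirement, if early deaths leave STRONG alone.

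Intent-to-treat and the feasibility outcomes are unaffected. The change should be made, but the trial does not depend on it.

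**What to change.** In Analytic approach:

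- Keep intent-to-treat as the leading analysis.
- Replace the adherent-only between-arm comparison with an exploratory complier-average causal effect that uses random assignment as the instrument and keeps every randomised patient, including those who stop. Count dietitian visits the same way in both arms, since usual care has no schedule from which to take a fraction. State that the exclusion restriction is doubtful because other STRONG components may act outside the visits.
- Run no adherent-only comparison of overall or progression-free survival. If one is wanted, start it from a 12-week landmark applied to both arms and label it non-randomised.
- Report associations between adherence and outcome descriptively, within STRONG.

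The cost is a change of wording, some added analysis, and a count of usual-care dietitian visits. The interval will be wider than that of the adherent subset, and the estimate carries an extra assumption. Recruitment and the primary outcomes do not change.

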#### Aim 1 analyses

Feasibility and acceptability outcomes will be summarized using descriptive statistics and compared against pre-planned benchmarks. We will use thematic analyses to analyze participant exit interview transcripts [124]. We will use a hybrid approach [125] for the thematic analyses by developing deductive codes based on the interview guide [126] and inductive codes that emerge from the data [127]. Two individuals will code all transcripts and come to a consensus regarding coding. We will use peer debriefs to discuss coding and interpretation, write memos to record reflections, and triangulate qualitative data with the quantitative data [128, 129]. Data gathered will be used to refine the implementation strategy in future studies.

#### Aim 2 analyses

Preliminary outcomes will be measured at three time points (baseline, 3-, and 6-months) for two groups (intervention and control). We will use linear mixed-effects models to estimate changes in PG-SGA scores between groups, as they account for dependence of longitudinal assessments and allow for patients with incomplete data to be included in analyses. The model will include fixed effects for time, group, and group X time. A group X time interaction will provide evidence for differential change by treatment groups. Randomization strata and any group differences not balanced through randomization procedures will be included as covariates in the model. Recruitment site (UNC, Moffitt) will be included as a random effect in the analyses. Mean differences will be compared against the threshold for a clinically significant difference in PG-SGA score (4-point change). A similar approach will be applied for other discrete or continuously measured outcomes using MCIDs when available. We will use generalized estimating equations (GEEs) to estimate whether the change in the proportion of patients with severe malnutrition (yes/no) over time differs between the intervention and control group. A similar approach will be applied for other binary outcomes. For time-to-event outcomes (i.e., survival), we will use a stratified Cox proportional hazards model (stratified by randomization strata) and adjusted for any characteristics not balanced across groups. The primary parameter of interest is the Cox Hazards Ratio (HR). We will test model assumptions (e.g., Schoenfield residuals) and adjust the statistical approach as needed (e.g., use of time-varying HR). We will model Kaplan-Meier curves by group assignment from baseline to 6-months.

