### Randomization

Patients (*N* = 80) will be 1:1 randomized to the STRONG program versus usual care. The study statistician will develop a randomization table using the randomization function in Stata (StataCorp. 2025. Stata Statistical Software: Release 19. College Station, TX: StataCorp LC.) that will be uploaded to REDCap^®^ (Research Electronic Data Capture). Randomization will be stratified based on cancer type and treatment modality (e.g., single versus multimodal treatment) to ensure groups are balanced on these factors, which may affect malnutrition risk. Block randomization (in variable block sizes of 4 and 6) will be used to maintain balance across groups and concealment. Outcome assessors and the study statistician will be blinded to group allocation.

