#### Sample size considerations

The goal of this pilot randomized controlled trial is to assess feasibility of study procedures and feasibility of the implementation strategy prior to a definitive hybrid implementation-effectiveness trial. We will recruit 80 patients, assuming 15% will be lost due to attrition based on our prior studies, leaving a sample size of 68 (34 patients per arm). Guidance for conducting pilot randomized trials suggests 25–35 participants per arm is sufficient to estimate feasibility outcomes, such as recruitment and retention, and to provide preliminary estimates of intervention effect and variation [130–132]. Consistent with NIH guidance, this pilot trial is not powered for definitive hypothesis testing; the sample size selection is based on the goal of estimating feasibility outcomes and providing preliminary intervention effect estimates [133]. Nonetheless, with 68 patients, the study is powered to estimate mean change in PG-SGA score with reasonable precision (CI ± 2.4–2.8 points) depending on the standard deviation assumption (6–7 based on prior studies) [107] and an assumption of *r*=-.55 based on prior studies [134]. 

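### Covariates are added to the Aim 2 models because they turn out unbalanced; this barely touches the PG-SGA change contrast but costs precision and stability in the Cox model

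*Protocol article*

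**What the plan says.** The Aim 2 analyses section fixes the covariates of the PG-SGA mixed model in one sentence: "Randomization strata and any group differences not balanced through randomization procedures will be included as covariates in the model". Recruitment site enters as a random effect. Baseline is one of three modelled time points, and the group-by-time interaction is the stated evidence of differential change. The Cox model is stratified by the randomization strata and is also "adjusted for any characteristics not balanced across groups". Other continuous outcomes, and other binary outcomes after the GEE for severe malnutrition, are to follow a similar approach. The section does not say whether the imbalance rule carries over to them.

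The strata were chosen for prognosis. The Randomization section says "Randomization will be stratified based on cancer type and treatment modality" and gives the reason: "to ensure groups are balanced on these factors, which may affect malnutrition risk". Under Participant and treatment characteristics the article adds: "Clinical characteristics that may affect nutritional status (e.g., cancer stage, comorbidities) will be abstracted from the EHR". Under the stated rule, a characteristic such as cancer stage enters a model only if it happens to differ between arms.

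**The concern.** Patients "will be 1:1 randomized to the STRONG program versus usual care" in variable blocks within strata. If that is carried out correctly, every remaining baseline difference is chance. A covariate is useful because it predicts the outcome, and an observed imbalance does not show that it does. The added part of the covariate set can therefore admit variables unrelated to outcome and omit related ones that happened to balance. Which model is fitted then depends on the realised data.

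At stake are the preliminary effect estimates meant to inform the definitive trial. How much is at stake differs by model, so the models have to be taken separately.

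**Working it through.** **The plan's own figures.** No figure is attached to the covariate rule. The nearest are the evaluable sample and the PG-SGA precision under Sample size considerations, and both reproduce.
- The plan states "assuming 15% will be lost due to attrition based on our prior studies": 80 × 0.85 = 68, or 34 per arm.
- Half-width = 1.96 × SD × √(1 − r²) × √(2/34), with |r| = 0.55 and an assumed 95% level. SD 6 gives 2.38 and SD 7 gives 2.78, matching ±2.4 to ±2.8. The sign of r does not matter here because it is squared.

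**How often the rule fires.** The article gives neither the number of characteristics nor a criterion. Assume k independent characteristics.
- Criterion p < 0.05: P(at least one) = 1 − 0.95^k. This is 23% for k = 5, 40% for k = 10 and 54% for k = 15. At p < 0.10 with k = 10 it is 1 − 0.90^10 = 65%.
- Criterion standardized difference > 0.2 with 40 per arm: 0.2/√(2/40) = 0.894, so each variable is flagged with probability 0.371. For k = 10 the expected number is 3.7 and P(at least one) is 99%. Over k = 5 to 15 the expected number is 1.9 to 5.6 and the probability 90% to 99.9%.

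With 10 characteristics, the criterion alone moves the expected number of added covariates from 10 × 0.05 = 0.5 to 3.7. Being flagged is not itself harm; that depends on the model.

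**PG-SGA mixed model.** Write Y(i,t) = β0 + β1·G(i) + β2(t) + β3(t)·G(i) + γ·X(i) + u(i) + e(i,t). No covariate-by-time term is stated. The change from baseline is

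Y(i,t) − Y(i,0) = β2(t) + β3(t)·G(i) + e(i,t) − e(i,0),

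so γ·X(i) drops out. Simulation agrees (assumed: 40 per arm, random intercept, 10 baseline variables of which 2 are prognostic, selection at a standardized difference > 0.2, 150 replicates).
- Complete data: the interaction estimate was the same with and without selected covariates (largest difference 2 × 10⁻¹⁴), with SE 1.136 either way.
- 15% dropout: mean shift 0.05 points and maximum 0.21, against the 4-point threshold (0.21/4 = 5%). SE was 1.214 with no covariates, 1.213 with imbalance-selected ones and 1.211 with pre-fixed prognostic ones.

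The cancellation is specific to change. It would not apply to an arm difference at a single visit, but the plan rests its evidence on the interaction.

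**Cox model.** Nothing cancels here. The article gives no event count; 8–16 events by 6 months (10–20% of 80) is assumed.
- Events per coefficient with treatment plus 3.7 selected covariates: 8/4.7 = 1.7 to 16/4.7 = 3.4. With treatment plus one named factor: 8/2 = 4 to 16/2 = 8.
- Simulation (assumed: 80 patients, about 14 events, 10 covariates): the empirical SD of the log hazard ratio was 0.61 unadjusted, 0.68 with imbalance-selected covariates and 0.61 with one pre-named prognostic factor. 0.68/0.61 = 1.11. As a 95% multiplicative margin on the hazard ratio, exp(1.96 × 0.61) = 3.3 becomes exp(1.96 × 0.68) = 3.8.
- The cost depends on how many variables are admitted. A strict cut-off admitting about 0.5 would cost much less than a lenient one.

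**GEE models.** With a non-linear link such as the logit (the link is not stated), a main-effect covariate does not cancel in this way. If the rule is applied there, the estimate again depends on which variables happened to differ. This was not quantified.

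**The case against.** The case for leaving the rule alone is substantial, and most of it stands. Strata, site and baseline PG-SGA are in the mixed model whatever the data show, so the adjustment does not ignore prognosis; the criticism reaches only the added covariates. For the PG-SGA change contrast the rule is almost inert. The study statistician is blinded to allocation, which limits deliberate choice, although arm-coded data still reveal imbalance and the model still varies with it. Aim 2 is secondary in a pilot expressly not powered for hypothesis testing, and the feasibility and acceptability results are descriptive and untouched. A candidate list and threshold may sit in an analysis plan that is not shown. That last point does not rescue the rule: a threshold would define imbalance more sharply but would still select on it.

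A reader might infer two stronger things that the document does not support.
- *That the rule forfeits the planned PG-SGA precision.* In a follow-up-score model (assumed: 34 per arm, 10 variables, 2 prognostic) the half-width is 2.39–2.78 with pre-fixed covariates and 2.86–3.42 with imbalance selection. The first range resembles the stated ±2.4 to ±2.8, but the protocol does not plan a follow-up-score model, so this loss cannot be charged to it.
- *That the rule inflates false positives.* In that same illustration type I error was 4.2% (p < 0.05 rule) and 3.5% (standardized difference > 0.2), which is slightly conservative.

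**Conclusion.** The concern holds in a limited form. The article states, in two places, a rule that selects additional covariates on chance imbalance instead of prognosis. For the PG-SGA group-by-time contrast the effect is nil with complete data and about 0.05 points on average with 15% dropout. In the Cox model the rule makes the adjusted hazard ratio depend on which variables happen to differ. An open-ended covariate set also asks more than 8–16 events can support; the illustrated cost is about 11% in the SD of the log hazard ratio. The GEE models may be affected if the rule extends to them.

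These sizes rest on assumed event counts, numbers of covariates and imbalance criteria, none of which the article gives. Progression-free survival cannot have fewer events than overall survival, so the problem may be milder there. This is a cheap improvement to secondary analyses and no threat to the pilot's primary aim.

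**What to change.** - Delete the imbalance trigger from both the mixed-model and the Cox sentences.
- Mixed model: keep the strata and site, and name now at most one or two further prognostic factors already being collected, for example cancer stage. Keep baseline PG-SGA as a modelled time point and do not also enter it as a covariate, which would use it twice.
- Survival: use the strata and at most one named factor.
- GEE and other outcome models: state that the same fixed list applies.
- Report baseline balance descriptively. Any adjustment for an observed imbalance belongs in a sensitivity analysis labelled as such.

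The cost is a rewording of two sentences, with no new data. The downside is that a chance imbalance in an unlisted variable is handled only in the sensitivity analysis. Little gain in PG-SGA precision should be expected, since main effects cancel there; the benefit is a model that can be written down in advance and a Cox estimate that does not move with chance differences.
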